**Discussion:**

The goal of this prospective randomized trial is to compare and to test improvement in wound healing, quality of life, safety/efficacy, cost-effectiveness, short and long-term outcomes and vein-graft patency after endoscopic open CO_2 _harvesting system versus conventional vein harvesting.

The expected results are of high clinical relevance and will show the safety/efficacy or non-inferiority of one treatment approach in terms of vein harvesting for coronary artery bypass grafting surgery.

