### Primary end points

We have two primary end points (see Appendix 1) with different deadlines:

• a short-term one (6 weeks after CABG surgery), regarding freedom from wound complications, defined as cellulitis, edema, ecchymosis, hematoma, cellulites, drainage, necrosis, dehiscence, debridement; leg wound infection according to ASEPSIS score;

• a long-term one (2 years after CABG surgery), regarding freedom from MACE, i.e. death, myocardial infarction, recurrent angina or congestive heart failure due to vein graft failure with assessment of vein-graft patency.

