**Figure 1 F1:**
[figure not shown]
**Flowchart of the study design**. This figure illustrates the study design.

All data relative to enrolled patients will be entered in a database containing preoperative demographics and risk factors (age, sex, BMI, morbidities, coronary artery lesions severity by SYNTAX score and surgical risk profile by EUROscore, etc), intra-operative variables (site of harvesting, number of incisions, lengths, times, etc), vein specific variables, pre- and post- harvesting respiratory and hemodynamic parameters, histological status of the harvested vein, as examined and graded by a pathologist. Wound healing and variables in the ASEPSIS score and other wound-related morbidities, wound complications, outcome and correlated events of the follow-up are to be evaluated by an independent clinical committee every 6 weeks in the first year, and then at 18 and 24 months. The total number of data characterizing each patient will be approximately 180, a complete scenario of his risk factors, surgical and post surgery history, short-, mid- and long-term outcome. The two cohorts will hence be described by two 115 × 180 arrays, with the intention to bring to light differences and similarities in behaviors and trends by means of a thorough statistical analysis.

The continuous data will be reported as average ± standard deviation and will be analyzed by standard ANOVA tests. Discrete or dichotomous values will be reported as percentages, risk ratios (and their 95% confidence intervals), and will be stratified in *mxn *contingency tables, analyzed for significant differences by chi-square tests (with Yates'correction in the case of 2 × 2 tables) and Fisher or mid-P tests.

The freedom from late wound complications and in general all event-free survival rates will be obtained according to the Kaplan-Meyer method, with the statistical differences among them estimated by the Mantel-Cox log-rank test. As usual, statistical significance will be determined at a *p *value (probability of null hypothesis: the observed differences are imputable to chance) ≤ 0.05, corresponding to the false positive probability (α or type I error). In case of a *p *value > 0.05, the next step will be the estimate of the test power *II *and the related false negative probability (β or type II error = 1- *II*).

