A few considerations on the selected sample size are opportune. Assuming the values conventionally accepted for the drop-out and cross-over rates of ≤ 10% and ≤ 5% of the patients, follow-up will see two cohorts of approximately 100 patients for each. This means that data computed as percentage within each cohort should be correctly reported with an uncertainty of ± 5%.

It is well known that the power of the statistical test used to carry out comparisons between two sets of data depends both on the sample sizes and the entity of the difference between data observed in the two groups. A tiny difference has difficulty to be evidenced as statistical significant even with a very large sample size, while a substantial difference can be easily assessed as significant even with a small sample size.

In a trial in which the analysis wants to take into account several outcomes, the presence of a wide range of observable differences makes very difficult a "valid-for-all" estimate of the sample size necessary to achieve the desired test power (usually 80%) or inversely on the test power predicted on the base of the actual sample size.

In our trial, as far as the short-term outcome is concerned, previous studies [8,9] suggest a six-week leg wound complication rate of about 20% in the CVH arm and less than 4% in the EVH arm. With this risk/prevalence difference of 16%, and the predicted sample size of 100, the power based on normal approximation is about 94% (91% if we apply the continuity correction), and thus very good: a power of about 80% would be reached already with a sample size around 80.

The situation changes dramatically when we consider the mid- and long term outcomes. Previously quoted studies [2] suggest a first-year vein-graft failure rate of about 20% with an annual occlusion rate of 1% to 2% in the first six years, with practically no difference between the EVH and CVH approaches. On the basis of previous comparative trials of EVH versus OVH, none of the clinically relevant cardiovascular outcomes differed significantly for EVH compared with OVH (Allen et al. [11] reported survival free of MACE at up to 5 years as 75% vs. 74%, p = 0.85). A 2-3% of non-inferiority margin is therefore planned in this protocol study. The 80% test power goal, with such small risk prevalence difference requires sample sizes of at lest 3000 for each cohort, values well beyond any practical implementation in a single medical centre, at least in a lifetime.

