## Discussion

Nowadays, a research to evidence benefits, harms and resource implications of EVH vs. OVH must not only meet the requirements of being prospective, randomized and including a great number of baseline, inter-operative, post-operative and follow-up co-founding variables, but needs also to exploit the latest improvements in the available technologies of vein harvesting.

The Endoscopic Saphenous harvesting with an Open CO_2 _System (ESOS) Trial, was configured after these guidelines.

Its primary goal is to compare and to quantify improvements in short and mid-term outcomes after endoscopic open CO_2 _harvesting (EVH) versus conventional open vein harvesting (CVH): safety/efficacy, leg wound infections and morbidity, patient satisfaction, short and long-term outcome, with histological and angiographic studies will be matter of thorough investigation.

The results on wound healing, mobility, patient satisfaction, health-related quality of life, safety/efficacy, cost-effectiveness are expected to be available shortly after the beginning of the trial. The mid-term outcomes and vein-graft patency will be estimated at the end of the 2-year follow-up, when a possible extension of the period of observation will also be considered.

A secondary goal of ESOS is to provide guidance to physicians on optimal CABG strategies for patients with different risk levels. A more widely spread and accurate knowledge on this issue may also help patients in their choices in a difficult predicament of their life when they have to take fundamental decisions for their health.

When compared to CVH procedure, EVH is expected to confer a 16% reduction in leg wound infections. If the use of new improved instrumentation will also improve the long-term event-free survival rate, as we hope, endoscopic saphenous vein harvesting should then be definitely recommended to patients with CAD, also for the high level of satisfaction usually reported by patients undergoing this minimally invasive procedure.

This study, besides providing new information aimed to improve the quality of care for CAD patients, will also assess the cost/effectiveness of this approach as far as in-patient and out-patient care is concerned.

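### No analysis stated in the article uses the planned 2-3% non-inferiority margin, and the power estimate prescribed after p > 0.05 adds no information

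*Protocol article*

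**What the plan says.** Under Primary end points, the second of two primary end points is "a long-term one (2 years after CABG surgery), regarding freedom from MACE". The Discussion part of the Abstract expects that the results "will show the safety/efficacy or non-inferiority of one treatment approach". The sample-size text in Trial Population, and Statistical Analysis states: "A 2-3% of non-inferiority margin is therefore planned in this protocol study".

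The same section fixes the analysis: "all event-free survival rates will be obtained according to the Kaplan-Meyer method, with the statistical differences among them estimated by the Mantel-Cox log-rank test". Significance is set at p ≤ 0.05, and p is glossed as the "probability of null hypothesis: the observed differences are imputable to chance". For a p "value > 0.05, the next step will be the estimate of the test power", together with the type II error.

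The only confidence intervals planned are 95% intervals for risk ratios of discrete or dichotomous data. They are not linked to the margin, which is stated in percentage points. The section concedes that a gap this small would need at least 3000 patients per cohort, and then accepts 115 per cohort, about 100 at the end of follow-up.

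**The concern.** A non-inferiority claim needs a confidence limit for the treatment difference set against a margin. The article names a margin (as a range) and the conclusion, but the test, the threshold and the follow-on step it fixes all address a different question, namely whether the arms differ. The follow-on step covers exactly the result most likely at this sample size, and it yields nothing usable.

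The outcome is a primary end point that includes death and myocardial infarction. The Background calls long-term results controversial and cites one analysis that pointed to harm (80% against 83% event-free at three years). The article also argues from non-significance itself: it cites a randomised comparison with 75% against 74% free of MACE, p = 0.85, and presents the margin as following from it. That study had 112 patients. Assuming 56 per arm, its 95% CI is about ±1.96 × √(0.75×0.25/56 + 0.74×0.26/56) = ±16 points, so it cannot establish similarity to within 2-3 points. Glossing p as the probability of the null hypothesis is incorrect and does not help a reader facing a large p.

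**Working it through.** **Inputs.** About 100 evaluable patients per arm, α = 0.05, 80% target power and a margin of 2-3 points (Trial Population, and Statistical Analysis). The Background gives event-free rates for conventional harvest of 74% at five years and 83% at three years, and for endoscopic harvest of 75% and 80%. No 2-year rate is given, so I assume 75%, 80% and 83% in turn. Sidedness of α is not stated; I take it as two-sided.

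**The article's own figures.** For 20% against 4% at 100 per arm, the normal approximation gives 94.2% power, and 91.1% with continuity correction. The article states 94% and 91%, so two-sided 0.05 is the right reading.

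For the long-term figure, n = [1.96√(2p̄(1−p̄)) + 0.8416√(p₁(1−p₁)+p₂(1−p₂))]² / d². With 80% against 77%, n = (1.139 + 0.489)² / 0.03² ≈ 2943 per arm (3009 with continuity correction), which matches the stated 3000. This is a formula for a test of difference, and it fits the 3-point end of the range only. The 80% base rate is my assumption.

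**What the power step returns.**

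- *At the observed difference.* The sample-size remarks say that power depends on sample size and on the difference seen between the groups, so this is the likely reading. Observed power = Φ(|z|−1.96) + Φ(−|z|−1.96), where z is fixed by p:

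| p | \|z\| | Observed power |
|---|---|---|
| 0.05 | 1.96 | 50% |
| 0.20 | 1.28 | 25% |
| 0.85 | 0.19 | 5% |

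- *At a 3-point difference.* For 83% against 80%, s₀ = √(2×0.815×0.185/100) = 0.0549 and s₁ = √((0.83×0.17+0.80×0.20)/100) = 0.0549. Power = Φ((0.03−1.96×0.0549)/0.0549) = Φ(−1.41) = 7.9%. The log-rank version, with 37 events and a hazard ratio of 1.20, also gives 7.9%. At 75% against 72% it is 6.9%. These values are known before the trial starts.

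**How often p > 0.05 when endoscopic harvest is truly worse** (100 per arm, same approximation, both tails counted):

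| Conventional event-free rate | 3 points worse | 5 points worse | 10 points worse |
|---|---|---|---|
| 75% | 92.3% | 87.6% | 66.2% |
| 80% | 91.9% | 86.5% | 62.9% |
| 83% | 91.5% | 85.6% | 60.0% |

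Two-year rates may be better than these 3- and 5-year rates. At 90% event-free, an assumption with no source in the article, the three figures become 90%, 81% and 48%.

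**What a margin test could do.** With equal true rates p and one-sided 0.025, SE = √(2p(1−p)/100) and power = Φ(margin/SE − 1.96):

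| Event-free rate | 95% CI half-width | Power, 2-point margin | Power, 3-point margin | n per arm for 80% power, 2 points | n per arm for 80% power, 3 points |
|---|---|---|---|---|---|
| 75% | 12.0 points | 5.1% | 7.1% | 7359 | 3271 |
| 80% | 11.1 points | 5.4% | 7.6% | 6280 | 2791 |
| 83% | 10.4 points | 5.7% | 8.1% | 5538 | 2462 |

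Moving from a 3-point to a 2-point margin multiplies the sample size by (3/2)² = 2.25, so the stated range is not a usable margin.

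**The case against.** Several objections have force.

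- *The article never says that non-inferiority will be judged by the log-rank test.* Correct. A reader might infer it, because that is the only comparison of event-free survival described, but the text assigns the test to differences and gives no decision rule for the margin. What the text shows is a margin that no stated analysis uses.
- *The power step does not itself reassure.* A reader might infer that it lets a non-significant result pass as equivalence. But power of about 50% or less means a type II error of about 50% or more, and the article frames the step as an estimate of the false-negative probability. If anything it would discourage that reading. The fault is that it is uninformative.
- *The difference at which power is computed is not stated.* True. The observed difference is only implied by the sample-size remarks, which is why both readings are worked through above.
- *The long-term aim is mixed.* The Abstract couples safety/efficacy with non-inferiority, and the main Discussion hopes for better event-free survival. A log-rank test suits that second aim, but it leaves the non-inferiority conclusion without an analysis.
- *Low power is already disclosed, and a margin test would have only 5-8% power.* True. The correction changes what may be claimed, not how much the trial can learn.
- *This is a condensed article and the analysis plan is not shown.* A margin test may exist there, so it cannot be said that the margin is never tested. The point stands for what the article itself fixes: the test, the threshold and the next step.

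**Conclusion.** The point holds for the article as written. It plans a non-inferiority margin and a possible non-inferiority conclusion for a primary end point, states no analysis that uses the margin, and prescribes a follow-on calculation that is either a restatement of p (at most about 50%) or a figure already known (about 8% at 3 points).

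At about 100 per arm, p > 0.05 is expected in about 92% of trials if endoscopic harvest is 3 points worse, 86-88% if 5 points worse and 60-66% if 10 points worse. A non-significant result therefore carries no support for non-inferiority. These figures rest on assumed event-free rates of 75-83% drawn from 3- and 5-year data, two-sided 0.05 and a normal approximation. The 90% event-free case gives somewhat lower figures and the same conclusion.

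**What to change.** In Trial Population, and Statistical Analysis:

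1. Delete the power estimate after p > 0.05.
2. Redefine p as the probability, if the null hypothesis is true, of a result at least as extreme as the one observed.
3. For the long-term primary end point, report the 2-year Kaplan-Meier difference in freedom from MACE, endoscopic minus conventional, with its 95% CI.
4. If a non-inferiority statement is kept, replace the 2-3% range by one fixed margin with its justification, and allow the statement only if the lower confidence limit lies above minus that margin.
5. State that p > 0.05 supports no conclusion of equivalence or non-inferiority.
6. Describe the long-term comparison as estimation, with an expected 95% CI of about ±10-12 points and about 5-8% power to show non-inferiority, and align the Abstract with this.

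The cost is wording only. The difference and its interval come from the Kaplan-Meier analysis already planned, with no change to recruitment, follow-up or data collection.

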**Methods/Design:**

**Endoscopic Saphenous harvesting with an Open CO_2 _System **trial includes two parallel vein harvesting arms in coronary artery bypass grafting surgery. It is an interventional, single centre, prospective, randomized, safety/efficacy, cost/effectiveness study, in adult patients with elective planned and first isolated coronary artery disease. A simple size of 100 patients for each arm will be required to achieve 80% statistical power, with a significant level of 0.05, for detecting most of the formulated hypotheses. A six-weeks leg wound complications rate was assumed to be 20% in the conventional arm and less of 4% in the endoscopic arm. Previously quoted studies suggest a first-year vein-graft failure rate of about 20% with an annual occlusion rate of 1% to 2% in the first six years, with practically no difference between the endoscopic and conventional approaches. Similarly, the results on event-free survival rates for the two arms have barely a 2-3% gap. Assuming a 10% drop-out rate and a 5% cross-over rate, the goal is to enrol 230 patients from a single Italian cardiac surgery centre.

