In the course of the trial all consecutive adult patients (18 years and older) with elective planned and first isolated coronary artery disease (CAD) amenable to coronary artery bypass grafting surgery will be screened to establish their eligibility to both EVH and CVH on the basis of the guidelines reported in Table 1.

Patients not amenable for both treatment options, or who are expected to have a better outcome with one of the two, will not be included in the trial; neither will be the patients who refuse to be randomized because of their personal preference for one approach over the other.

Patients deemed amenable for both harvesting modalities, after having signed the informed consent, will be assigned by means of a standard web-based computer generated randomization scheme to one of the two cohorts, either EVH or CVH, and after allocation they will be included in the intention to treat analysis. An independent clinical research assistant will be responsible for randomization and treatment assignment.

The post surgery follow-up will consist of clinic visits on the sixth week after CABG surgery and at occurrence of any adverse event. Each information leading to in-patient or out-patient treatment regarding major adverse cardiac events, vein-graft failure or occlusion or other morbidity, will be collected. The number of visits required to clear up each wound complication will be used as a surrogate to determine outpatient resource utilization for wound management.

Follow-up angiograms will be performed at 18 months to explore directly vein graft longevity. This will allow not to rely totally on the indirect, and sometimes deceiving, information supplied by the event-free survival rates.

Follow-up will stretch over a minimum of 24 months. At the end of this period there will be an assessment of the state of the art based on the results obtained with the two different approaches, whose rationale will lead to the decision to either conclude or continue the follow-up.

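### Cross-overs are subtracted from the sample as if lost, although the analysis is by intention to treat, so the stated 94% (91%) power is modestly overstated

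*Protocol article*

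**What the plan says.** Three statements in the protocol article bear on this.

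- **Attrition.** Under Trial Population, and Statistical Analysis, the plan assumes "drop-out and cross-over rates of ≤ 10% and ≤ 5% of the patients, follow-up will see two cohorts of approximately 100 patients" in each arm. The abstract uses the same two rates to reach the recruitment total: "Assuming a 10% drop-out rate and a 5% cross-over rate, the goal is to enrol 230 patients".
- **Power.** The same section takes a "six-week leg wound complication rate of about 20% in the CVH arm and less than 4% in the EVH arm". It applies the resulting 16-point gap at 100 patients per arm and reports that "the power based on normal approximation is about 94% (91% if we apply the continuity correction").
- **Analysis set.** The text after Table 1, under Secondary end points, says of randomised patients that "after allocation they will be included in the intention to treat analysis".

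The expected difference is nowhere reduced for cross-over. The protocol also does not say in which direction patients are expected to cross, or whether the 5% applies to each arm or to the trial as a whole.

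**The concern.** Drop-out and cross-over affect an intention-to-treat comparison differently. A drop-out with no outcome reduces the number analysed. A cross-over still has an outcome, is counted in the allocated arm, and carries roughly the risk of the harvest actually received. The number analysed does not fall, but the two arms' expected rates move together.

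The plan treats both as losses and leaves the 16-point difference intact. Its power figure therefore describes a comparison from which cross-overs are absent, which is not the stated analysis.

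This matters mainly because the six-week end point is the primary end point that the trial can answer. The same section says that the long-term one would need at least 3000 patients per cohort. The one power statement that supports the sample size should describe the analysis that will be done.

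**Working it through.** **Inputs from the protocol article**

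- Event rates: CVH 20%, EVH 4% (the protocol gives 4% as an upper bound).
- Recruited: 115 per arm. Planned at end point: about 100 per arm.
- Drop-out at most 10%, cross-over at most 5%.
- Significance: "with a significant level of 0.05".
- Test for 2 × 2 tables: "analyzed for significant differences by chi-square tests (with Yates'correction" in that case.

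**Assumptions.** The test is two-sided. The protocol does not say so, but the two-sided formula reproduces its figures, while a one-sided test would give 97.1%. A cross-over takes the event rate of the harvest received.

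**Step 1. How 115 becomes about 100**

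- Adding the two rates: 100 × 1.15 = 115.
- Removing both: 115 × 0.85 = 97.75, or 115 × 0.90 × 0.95 = 98.3.
- Removing drop-out only: 115 × 0.90 = 103.5, taken as 103.

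The planned figures fit removal of both groups.

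**Step 2. Reproduce the stated power**

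With d = p1 − p2, p̄ = (p1 + p2)/2, SE0 = √[2p̄(1 − p̄)/n] and SE1 = √[p1(1 − p1)/n + p2(1 − p2)/n]:

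- Power = Φ[(d − 1.96 × SE0)/SE1].
- With continuity correction, d is replaced by d − 1/n.

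At n = 100, 20% vs 4%: d = 0.160, SE0 = 0.04596, SE1 = 0.04454.

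- Uncorrected: Φ(1.570) = 94.2%.
- Corrected: Φ(1.345) = 91.1%.

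These match the stated 94% and 91%, so no dilution was applied.

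**Step 3. Keep cross-overs in their allocated arm**

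Let c1 be the share crossing from CVH to EVH, and c2 the share crossing from EVH to CVH.

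- CVH rate = (1 − c1) × 0.20 + c1 × 0.04
- EVH rate = (1 − c2) × 0.04 + c2 × 0.20

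For 5% in both arms: 0.95 × 0.20 + 0.05 × 0.04 = 0.192 and 0.95 × 0.04 + 0.05 × 0.20 = 0.048, so d = 0.144. At n = 103, SE0 = 0.04528 and SE1 = 0.04416. Power is Φ(1.251) = 89.5%, or Φ(1.031) = 84.9% corrected.

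All four readings of the 5%, at 103 per arm:

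| Cross-over assumed | CVH vs EVH | Power | With correction |
|---|---|---|---|
| 5% in both arms | 19.2% vs 4.8% | 89.5% | 84.9% |
| 5%, EVH to CVH only | 20.0% vs 4.8% | 91.7% | 87.9% |
| 2.5% in each arm | 19.6% vs 4.4% | 92.5% | 88.8% |
| 5%, CVH to EVH only | 19.2% vs 4.0% | 93.2% | 89.7% |

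**Step 4. Size of the overstatement**

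- Uncorrected: from 94.2 − 93.2 = 1.0 to 94.2 − 89.5 = 4.7 points.
- Corrected: from 91.1 − 89.7 = 1.4 to 91.1 − 84.9 = 6.2 points.

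Keeping the cross-overs adds about 3 to 5 patients per arm, which offsets part of the dilution.

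**The case against.** The strongest reply is that the other inputs are already cautious. Both attrition rates are ceilings, and the EVH rate is given as below 4%. If the EVH rate were 3% (an illustrative assumption), 5% cross-over in both arms at 103 per arm would still give about 93.7% (90.3% corrected). A 10% loss is also a lot for a six-week end point. With all 115 per arm retained and 5% crossing only from EVH to CVH, power is 94.3% (91.5%), in line with the stated figure. This stands as a reason to call the overstatement modest and to give a range. It does not remove the error, because the plan itself uses 4% and about 100 per arm in this calculation, and on those inputs the dilution is left out. Caution in one input is not a statement about another.

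A second reply is that no decision changes. That is right: power exceeds 80% in every case, and the protocol also justifies its size by resources.

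Two stronger readings are tempting, and the document supports neither.

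- A reader might infer that cross-overs will be left out of the analysis, which would undo the randomisation. The figure of about 100 is a planning count, not a rule for the analysis set. No text plans such an exclusion, the intention-to-treat statement points the other way, and the data are described as two full arrays of 115 patients.
- A reader might take 89% (85%) as the correct power. That is the least favourable of the four readings of the 5%, and the protocol does not settle on it.

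**Conclusion.** The inconsistency is real and its effect is modest. The stated power does not belong to the stated analysis. On the plan's own rates and its 10% drop-out, power under intention to treat is 89.5% to 93.2%, or 84.9% to 89.7% with continuity correction. The corrected range is the more relevant one, since Yates' correction is planned for 2 × 2 tables. The six-week end point is not underpowered.

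The result rests on a two-sided 5% test, on cross-overs having the risk of the harvest received, and on cross-over at its 5% ceiling. Less cross-over would shrink the gap.

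**What to change.** In the sample-size paragraph, and in line with it in the abstract:

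1. Count only drop-outs as attrition: 115 × 0.90, about 103 per arm.
2. Apply the assumed cross-over as dilution of the 16-point difference, and state as an assumption its direction and whether the 5% is per arm or overall.
3. Restate the power for the six-week end point as about 89–93% (85–90% with continuity correction), or as the single matching figure once the cross-over assumption is fixed.

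The total of 230 does not change. The cost is two or three sentences and a stated power about 1 to 5 points lower (1 to 6 with correction).

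### The abstract's claim that 100 per arm gives 80% power for most hypotheses is not supported by the article's own calculations; the size of around 80 for the wound end point is also loosely stated

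*Protocol article*

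**What the plan says.** The abstract (Methods/Design) says: "A simple size of 100 patients for each arm will be required to achieve 80% statistical power". It sets alpha at 0.05 and applies the statement to most of the hypotheses that the trial sets out. Its next sentence gives the assumed wound complication rates, 20% for conventional harvesting (CVH) and under 4% for endoscopic harvesting (EVH).

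The body (Trial Population, and Statistical Analysis) treats the two primary end points separately.

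- **Short term.** It assumes a "six-week leg wound complication rate of about 20% in the CVH arm and less than 4% in the EVH arm". For 100 per arm and the 16-point gap between those rates, it reports that "the power based on normal approximation is about 94% (91% if we apply the continuity correction", and adds that "a power of about 80% would be reached already with a sample size around 80".
- **Long term.** It plans a non-inferiority margin of 2-3% and says that 80% power for so small a difference needs 3000 or more per cohort, which it calls out of reach for one centre.

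The same section says that one size serving every outcome is very hard to give. It plans chi-square tests with Yates' correction for 2 × 2 tables, and also names Fisher and mid-P tests.

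**The concern.** The abstract makes one power statement for the trial as a whole, while the body gives two very different answers for the two primary end points. If the body is right, 100 per arm is more than 80% power requires for one primary end point and far too few for the other. A reader who sees only the abstract would take a neutral long-term result as coming from a trial with 80% power, which the article itself says it does not have.

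Separately, the body gives a power at 100 per arm and a size for 80% power from the same inputs. The two should come from the same formula, and it is worth checking that they do.

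**Working it through.** **Inputs.** CVH rate p1 = 0.20 and EVH rate p2 = 0.04 (body; the article says less than 4%, so 0.04 is the upper end). Alpha 0.05 (abstract). Equal arms. Sidedness is not stated; two-sided is assumed and tested in step 1.

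**Common quantities.** d = 0.16 and the mean rate is 0.12.

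- Null term: √(2 × 0.12 × 0.88) = √0.2112 = 0.4596; times 1.960 = 0.9007.
- Alternative term: √(0.20 × 0.80 + 0.04 × 0.96) = √0.1984 = 0.4454.

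**Step 1: reproduce the stated power at 100 per arm.**

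Power = Φ[(d√n − 0.9007) / 0.4454]. For the continuity correction, d is replaced by d − 1/n.

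- Uncorrected: (1.600 − 0.9007) / 0.4454 = 1.570, power 94.2%. The article says about 94%.
- Corrected: (1.500 − 0.9007) / 0.4454 = 1.345, power 91.1%. The article says 91%.

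One-sided testing would give 97.1% and 95.3%. The published pair therefore points to the two-sided pooled normal approximation.

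**Step 2: size for 80% power by the same formula.**

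- Uncorrected: n = (0.9007 + 0.8416 × 0.4454)² / 0.16² = 1.2756² / 0.0256 = 63.6, so **64 per arm** (power 80.3%).
- Corrected: n = (63.56 / 4) × [1 + √(1 + 4 / (63.56 × 0.16))]² = 15.89 × 2.1804² = 75.5, so **76 per arm** (power 80.3%).

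**Step 3: power at the stated 80 per arm.**

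- Uncorrected: (0.16 × 8.944 − 0.9007) / 0.4454 = 1.191, power 88.3%.
- Corrected: (0.1475 × 8.944 − 0.9007) / 0.4454 = 0.940, power 82.6%.
- Exact power at 80 is 84.7% for the Yates-corrected test and 86.8% for Fisher's test.

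**Step 4: other routes to 80.** The unpooled variance gives 61 (73 corrected), the arcsine method 58, and one-sided testing 50 (62 corrected). A rate below 4% lowers the number further. Diluting both arms by 5% cross-over (19.2% v 4.8%) gives 79. The article does not describe this step; it counts cross-over in going from 115 to about 100. The dilution would also break the published power at 100: (0.144 × 10 − 0.9007) / √(0.192 × 0.808 + 0.048 × 0.952) = 0.5393 / 0.4481 = 1.203, or 88.6% instead of 94%.

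**Step 5: set the abstract against the body.**

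| Primary end point | Power at 100 per arm | Size per arm for 80% power |
|---|---|---|
| Six-week wound complications | 94% (91% corrected), stated and reproduced | around 80 stated; 64 (76 corrected) computed |
| Long-term outcome | not stated | 3000 or more, stated |

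Neither row gives 100 as the 80%-power size. The long-term requirement is 3000 / 100 = 30 times the planned evaluable number. No power calculation is shown for any other hypothesis.

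**The case against.** Several points count on the other side.

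- **The size was a compromise, and the article says so.** It presents 115 per cohort as balancing statistical needs against resources, states the wound end point's power correctly, and admits that the long-term comparison is out of reach. This stands: the body is candid and its operative figures are sound. It does not rescue the abstract, which says something else.
- **The figure of 80 is hedged and close to the relevant calculation.** It is given as an approximate size for an approximate power, directly after the continuity-corrected 91%, and the planned 2 × 2 test is Yates-corrected. Against 76 it is 4 patients high, a loose rounding in the safe direction. This largely stands. The miss is clear only against the uncorrected 64, the version behind the leading 94%.
- **Nothing in the conduct of the trial depends on it.** About 100 evaluable patients per arm exceeds both 64 and 76. This also stands.

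A reader might infer that the abstract's 100 and the body's 80 are two conflicting sizes for one comparison. The article does not support that. The abstract ties its 100 to most of the hypotheses and does not name the wound end point in that sentence; the wound rates come in the next one. A reader might also infer that the wound comparison is short of power, which is the opposite of what the figures show.

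**Conclusion.** The point holds as an error in the stated power, of minor consequence. The abstract's general claim of 80% power at 100 per arm has no supporting calculation in the article: power is 94% (91% corrected) for the wound end point, and the article's own estimate for the long-term outcome is at least 3000 per cohort. The claim could still be true of some secondary hypotheses, for which no figures are shown, but it describes neither primary end point.

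As a lesser point, the size of around 80 should be 64, or 76 with continuity correction. The stated value is 25% above the first (80 / 64) and 5% above the second (80 / 76), so the error is conservative.

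This rests on two-sided testing, which the reproduced 94% and 91% support, on an EVH rate of exactly 4%, and on the figure of 3000 as the article states it, which was not re-derived here.

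**What to change.** In the abstract, replace the general 80% claim by a statement that 100 per arm gives about 94% power (91% with continuity correction) for the six-week wound end point at 20% v 4%, two-sided 0.05. Add that the trial is not powered for the long-term end point, for which the article's own estimate is at least 3000 per cohort.

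In Trial Population, and Statistical Analysis, replace the size of around 80 by 64 per arm by the normal approximation, or 76 with the continuity correction, and say that the latter matches the planned Yates-corrected test.

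The cost is a few sentences of wording. Enrolment stays at 115 per cohort and the analysis is unchanged. The only loss is the abstract's general power claim.
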